### MET therapists

The MET therapists, who work in an “on-call” capacity, are Masters-level counselors, with degrees in psychology, social work, or a closely related field and prior clinical experience. All MET therapists have experience working with abused women and/or receive formal domestic violence training. METs therapists are trained for two days on using the treatment manual by a Motivational Interviewing specialist who is a member of the Certified Network of Motivational Interviewing Trainers. Prior to conducting an MET session with a study participant, the MET therapist conducts 2–3 practice sessions with ED patients – focusing on IPV and/or alcohol consumption. Practice tapes are rated for adherence by the Motivational Interviewing clinical supervisor. MET therapists are only added to the on-call schedule once they are consistently adherent to the intervention. Additionally, MET therapists receive ongoing clinical supervision from a doctoral-level social worker trained in Motivational Interviewing. Supervision occurs weekly, in a group format. During supervision, recordings of MET sessions are reviewed for adherence to the MET protocol. Motivational Interviewing expert, [name], reviews a randomly selected 10% of all audiotapes, to provide on-going monitoring for adherence to the treatment manual. After study enrollment is complete, all recordings will be sent to [name] team of PhD-level Motivational Interviewing experts for full adherence ratings, along with reliability and inter-rater reliability calculations.

### Research assistants: training & supervision

Research Assistants (RAs) are part-time research employees who work in the EDs during data collection periods. Their primary responsibilities include screening, assessing for eligibility, consenting and enrolling patients, administering the demographic form and the Women’s Health Interview, and enrolling participants in the Interactive Voice Response System. RA training involves human subjects certification, in-depth review of the study protocol, and role-playing all components of the study engagement and enrollment process. All staff must attend a 3-day intensive training that covers IPV safety issues and reviews project background and procedural information. When ready for the ED setting, they first observe/shadow a senior RA and then conduct study and enrollment procedures under the observation of the clinical coordinator prior to screening on their own. On-going periodic shadowing by the supervising on-site coordinator ensures rigorous fidelity to the study protocol, as well as regular performance feedback from the project manager. RAs attend bi-weekly meetings with the coordinators, project manager and PI, where they share their experiences, problems, and brainstorm solutions. Refreshers on specific study procedures also occur during these regular staff meetings.

### Data management and quality assurance

The data collection tools for this study are varied; however, all study outcome data is stored and entered electronically using REDCap. REDCap is a secure web-based application designed to support data capture for research studies, providing an intuitive interface for validated data entry and automated export procedures for seamless data downloads to common statistical packages [33]. In addition, all databases are password-protected, stored, and backed up daily on a protected server.

The Data Manager and statistician developed a duplicate data entry plan for all collected study data. Every six months, a comparison of the data entered in the Initial and Duplicate databases is conducted using SAS Proc Compare report [34] and then research staff manually review inconsistent observations using the paper case files. An error rate is calculated using all founded inaccuracies in the Initial database. All inaccuracies are corrected in the initial database. Since primary outcome data is located throughout the data collection tools, 100% of case files are entered into the Duplicate database and compared to determine if the error rate is above 5%, the threshold for additional double data entry. To date, the error rate is less than 1%.

### Statistical analysis

#### Analysis across all three groups

With a goal of identifying the impact of assessment alone, the outcomes below can be analyzed across all three groups: the Brief Intervention Group (BIG), the Assessed Control Group (ACG) and the no contact control group (NCCG) using a intent-to-treat analysis that includes all participants who complete randomization and enrollment procedures and provide baseline and/or at least one follow up data collection point. Analysis across all groups including the no contact control group (NCCG) will include eligibility assessment data (baseline) and 3-month interview data collected on CTS2S and the AUDIT assessments.

Alcohol outcome measures are the frequency of heavy drinking (4 or more drinks/day for women) collected at baseline in person and by phone interview at 3 months using one item on the AUDIT [22], to calculate the frequency of 4 or more drinks. The full AUDIT score (0–40) [22] and additional drinking data are collected using a calendar-based Timeline Followback [35] for the month (28 days) prior to the interview.

IPV outcome measures include the frequency of IPV incidents (emotional, physical, and sexual) collected at baseline and by phone interview at 3 months using the CTS2S [23], scored 0–96. These data are on a likert scale, capturing a range of frequencies of occurrence in the previous three months. IPV Severity is calculated as the number of IPV incidents classified as severe in the preceding 3 months measured using specific items on the CTS2S [23]. IPV type and severity is also captured through the Composite Abuse Scale [36], scored 0–150.

All of the above measures are collected at baseline and 3, 6, and 12 months for the Intervention and Assessed Control Group and at 3 months only for the Non-Assessed Control Group. So any comparison across all 3 groups is limited to 3 month outcomes.

Using the intent-to-treat analysis for all patients who complete enrollment as described above, we will rely on generalized linear modeling to examine baseline and 3-month responses, adjusting for any other covariates that are determined to be significant in the preliminary analyses. Through pair-wise comparisons, this analysis will also compare 3 month differences between the assessed control group and no contact control group to determine the impact of assessment on the outcomes. For the analyses of the impact of assessment bias, only participants with 3-month outcome data will be included analysis.

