### Consent & randomization

Prior to consent, patients are informed that the enrollment process could take up to an hour to complete, whether or not they are discharged from the ED. Using the SPSS pseudorandom number generator [24], the study statistician created a block randomization scheme, in groups of 20, to determine study assignment. The project manager used the scheme to prepare two sets of opaque envelopes – one for each ED – that are indistinguishable from each other and thick enough so that their contents are not legible from the outside. All patients who give consent for participation are randomized by pulling the next sequential envelope. This process ensures that those who enroll participants are unaware of group assignment until after they are consented to be in the study; only the project manager and statistician are aware of the randomization scheme. For patients randomized to the intervention group, the RA presents a secondary consent for audio-recording of the motivational interview. Participants do not have to consent to audio-taping to participate in the study.

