### Structured women’s health interview

The women’s health interview is an extensive assessment, which includes a variety of validated measures for secondary outcomes, mediators and moderators (See Additional file 1: Table S1). Participants in the intervention and assessed control group are administered the interview at baseline, 3 months, 6 months, and 12 months. The no contact control participants only complete the interview at 3 months. All interviews are structured with close coded responses to validated questionnaires and take approximately 30 minutes to complete. Follow up interviews can be conducted over the phone or in person. RAs conducting follow up interviews are blinded to the participant’s group assignment during data collection. At the completion of all data collection, control group participants are offered an opportunity to receive the intervention, which is usually scheduled as a phone session by one of the motivational therapists.

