### Interactive voice response system

Participants in the assessed control group and intervention group complete a weekly phone survey measuring frequency of abuse or violence in their relationship, and consumption of alcoholic beverages. The first call is conducted in the ED at the time of enrollment. Participants call the toll-free number, which is open twenty-four hours a day, seven days a week, using a patient number and unique password to protect confidentiality. Prior to entering the password, anyone who calls the telephone number for the survey will hear only a generic message that does not refer to a study of IPV or alcohol.

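### In the three-group analysis, the set called intent-to-treat depends on completing enrolment after randomisation, and the assessment-reactivity contrast keeps only 3-month completers

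*Protocol article*

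**What the plan says.** Under 'Consent & randomization', the article states: "All patients who give consent for participation are randomized by pulling the next sequential envelope". Before consenting, "patients are informed that the enrollment process could take up to an hour to complete".

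The steps described for the time of enrolment differ by arm. Under 'Structured women's health interview': "Participants in the intervention and assessed control group are administered the interview at baseline, 3 months, 6 months, and 12 months", whereas "The no contact control participants only complete the interview at 3 months". The interview takes about 30 minutes. Under 'Interactive voice response system': "Participants in the assessed control group and intervention group complete a weekly phone survey", and the first call is made in the ED at enrolment. No such survey is described for the no-contact arm.

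The section 'Analysis across all three groups' calls its analysis intent-to-treat and says that it "includes all participants who complete randomization and enrollment procedures and provide baseline and/or at least one follow up data collection point". The modelling paragraph repeats the condition: "Using the intent-to-treat analysis for all patients who complete enrollment as described above". That paragraph ends by narrowing the set for the assessment question: "only participants with 3-month outcome data will be included analysis".

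**The concern.** An intent-to-treat set is fixed by randomisation. Here, membership also depends on finishing steps that come after the envelope is opened, and those steps are longer in the assessed arms. A woman who leaves the ED part-way could be left out of an assessed arm, while a similar woman in the no-contact arm, with less to complete, would be kept. Early departure is foreseeable: 'Screening and subject recruitment' already provides for eligible women who cannot stay.

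The second rule conditions on retention to month 3. Assessed women have weekly surveys, coordinator contact after missed calls, and a contact plan updated at every contact ('Retention'). No-contact women are not interviewed until month 3. The article describes the population as transient and hard to reach. If assessment changes who can be found at 3 months, a completer contrast mixes an effect on retention with an effect on drinking and violence.

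At stake is the question the no-contact arm exists to answer. 'Setting, timeline, and general study design' gives its purpose as judging how far improvement in the other arms may be due to assessment reactivity.

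**Working it through.** **Who is in each set**

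| Rule | Where stated | Who can drop out of the set |
|---|---|---|
| All consenting women randomised | Consent & randomization | Nobody |
| Must complete enrolment procedures | Analysis across all three groups | Women who stop after the envelope |
| Must have baseline and/or one follow-up point | Same | Almost nobody |
| Must have 3-month data (assessment contrast) | Same, end of modelling paragraph | All women lost by 3 months |

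The third rule removes almost nobody because this section counts the eligibility AUDIT and CTS2S as baseline, and those are taken before randomisation. The second and fourth rules do the excluding. The article does not give the number who stop during enrolment, so the second rule cannot be sized.

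**The plan's own counts**

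'Power for analyses' assumes up to 30% attrition:
- No-contact: 120 × 0.70 = 84
- Assessed control: 240 × 0.70 = 168

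These match the stated 84 vs. 168. The completer contrast then uses 84 + 168 = 252 of 360 randomised women and leaves out 36 + 72 = 108 (30%).

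The stated 80% power at d = 0.33 (two-sided 0.05) does not reproduce at these sizes: a normal approximation gives 69.5%. That is a separate matter, and nothing here depends on it.

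**Illustrative bias (assumed inputs)**

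Let m be the share of an arm missing and g the outcome gap, in SD, between its missing and observed women. The observed mean differs from the full-arm mean by m × g, so the bias in the contrast has size

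m₁g₁ − m₂g₂.

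The gap must be what remains after baseline adjustment. No value of g, and no split of attrition by arm, is in the document.

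| Missing, arm 1 / arm 2 | Gap, arm 1 / arm 2 | Bias (SD) | Share of d = 0.33 |
|---|---|---|---|
| 30% / 30% | 0.5 / 0.5 | 0.15 − 0.15 = 0 | 0% |
| 30% / 20% | 0.5 / 0.5 | 0.15 − 0.10 = 0.05 | 15% |
| 30% / 10% | 0.5 / 0.5 | 0.15 − 0.05 = 0.10 | 30% |
| 30% / 30% | 0.5 / 0 | 0.15 − 0 = 0.15 | 45% |

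**Effect on the test when there is no true difference**

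Holding the group sizes at 84 and 168, SE = √(1/84 + 1/168) = 0.134 SD. With z = bias / SE, the chance of a significant two-sided 5% result is 1 − Φ(1.96 − z) + Φ(−1.96 − z):
- 0.05 SD: z = 0.37, 6.6%
- 0.10 SD: z = 0.75, 11.6%
- 0.15 SD: z = 1.12, 20.2%

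In the 30% / 10% row, if the no-contact arm has the larger loss, the sizes would be 84 and 240 × 0.90 = 216. The 11.6% then becomes 12.2%, so the simplification matters little.

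**The case against.** **The wording may be looser than it looks.** Enrolment procedures are not defined, and elsewhere the article treats the 600 enrolled as the 240, 240 and 120 randomised. The phrase could simply mean randomised and enrolled, and no figure shows anyone lost between the envelope and the end of enrolment. This stands as a limit on size. It does not remove the problem: the condition is stated twice, and the steps described after the envelope do differ by arm.

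**The no-contact arm is not free of burden or follow-up effort.** The demographic form is collected from all participants, and a contact plan is made at enrolment. Scheduling two weeks ahead and updating contact details at ED return visits are described for participants generally, and reminders follow only missed calls. So the difference between arms is one of degree.

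**Completers can give a valid answer.** The plan models baseline and 3-month responses with covariates. If 3-month data are missing at random given those covariates, the completer contrast can be unbiased. With one follow-up point, likelihood or imputation from the same baseline variables rests on the same assumption and gives essentially the same contrast. This stands, and it means that changing the estimation method is not enough by itself.

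**Stronger readings that a reader might infer.**
- That the primary result is affected too. Both rules sit in the three-group section. The weekly intervention versus assessed control analysis is described separately, without either rule and with a planned pattern-mixture analysis, so its effect target is also not the benchmark here.
- That women who miss the therapy session are excluded. The session is the intervention, delivered by therapists. It is not among the research assistants' enrolment tasks, and no text makes it a condition of analysis. Refusing the recording consent excludes nobody.

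**Conclusion.** The point holds for the three-group analysis only. The set labelled intent-to-treat carries a post-randomisation condition that can differ by arm, and the assessed versus no-contact contrast is further limited to 3-month completers. Both are rules that the article states, not detail left to another document. The one missing-data sensitivity analysis described is for the weekly models, which leave out the no-contact arm.

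The firm figure is 108 of 360 women outside the reactivity contrast at the protocol's 30% attrition. A reader might infer that the contrast is therefore biased, but the document does not support that. Bias requires unequal loss, or unequal gaps between lost and observed women, beyond what baseline explains. The illustrations run from 0 to 0.15 SD against a target of 0.33. They rest on an assumed 0.5 SD gap and, in two rows, an assumed unequal loss. They show that a material bias is possible, not that one is present. That enrolment burden differs by arm is inferred from the described steps, because the article does not list what completing enrolment means.

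**What to change.** For the three-group analysis:

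1. Define the set as every randomised woman in her assigned arm, whether or not enrolment steps were completed. If the enrolment condition is kept for a secondary analysis, define it and call that set modified intent-to-treat.
2. Use the eligibility AUDIT and CTS2S, taken before randomisation, as baseline for all three arms.
3. Report, by arm, losses between randomisation and completed enrolment, and losses at 3 months.
4. Analyse 3-month outcomes by likelihood or multiple imputation using baseline variables, stating the missing-at-random assumption.
5. Add a sensitivity analysis for data not missing at random, delta-adjusted or pattern-mixture as already planned for the weekly models. Let the shift differ by arm, since equal shifts with equal loss cancel. This step is essential, because step 4 alone relies on the same assumption as a baseline-adjusted completer analysis.
6. Keep the 3-month completer analysis as supportive, labelled as such.

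The cost is revised wording and some added analysis. No new data collection is needed: the eligibility measures are already taken. The article says follow-up was still under way, so the rule could be changed before the final analysis.

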### Analysis of intervention and assessed control groups

We will compare the Intervention and Assessed Control Groups on primary outcomes of heavy drinking and incidents of IPV collected via the interactive voice response system for 12 weeks after enrollment and by interview at 3, 6 and 12 months.

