**Methods and design:**

We are completing data collection for a randomized controlled trial enrolling 600 female patients, age 18–64, presenting to one of two urban Emergency Departments, who self-disclose both problem drinking and intimate partner violence. Eligible patients are randomized to a brief manual-guided motivational intervention, and a phone booster at 10 days. The intervention, which is delivered by masters-level therapists during the Emergency Department visit, is recorded and monitored for fidelity. Primary outcomes are episodes of heavy drinking and incidents of intimate partner violence, assessed weekly by Interactive Voice Response System for 12 weeks and at 3, 6 and 12 months by interviewers blinded to group assignment. To identify the impact of assessment alone, we included a no-contact control group assessed only once at 3 months. Secondary outcomes include violence severity, changes in the Composite Abuse Scale and alcohol quantity/frequency, along with other health-related behaviors. The analysis will also explore the impact of likely mediators and moderators of the intervention.

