### Study hypotheses

● At-risk women who receive a brief motivational intervention – compared to an identically-assessed usual care group will have a reduction in days of heavy drinking (4 or more drinks/day) and incidents of IPV-assessed weekly for 3 months and by follow up interviews at 3, 6, and 12 months.

● Women’s self-efficacy, readiness to change, and rates of engagement with informal and formal social support systems will mediate the effect of the intervention on our primary outcomes.

● PTSD, a history of childhood sexual abuse, higher baseline severity of IPV and dependent drinking will moderate or reduce the effectiveness of the brief intervention.

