### Primary outcomes collected by the interactive voice response system

1. **Days of Heavy Drinking:** For this comparison, the AUDIT-C [25] heavy drinking question is asked, but is captured in the Interactive Voice Response System as the number of days when 4 or more drinks were consumed in the last week.

2. **Number of IPV events:** The 8 CTS2S [23] victimization questions are used to measure the incidence of IPV, and counts are collected for these questions each week via the interactive voice response system.

Our primary analytic method for the two group longitudinal comparisons will include implementing Hierarchical Generalized Linear Models (HGLM) to accommodate the clustering of the weekly repeated measures, as well as the nature of the outcome, which counts the number of heavy drinking days and the incidences of IPV per week. If the outcome measure displays a large proportion of zeroes, we will implement zero-inflated Poisson or zero-inflated Negative Binomial models, as appropriate with random effects. These models accommodate the clustering as well as the stack of zeroes present across the repeated assessments. [38] To assess the sensitivity of treatment effect estimates to missing data, we propose to fit the hierarchical regression models without accounting for informative missing data, and then compare these results with those from analyses that adjust for informative missing data. We will employ the pattern-mixture approach as applied to hierarchical regression models by Hedeker et al (1997). [39] Their methods assess whether important terms depend on certain missing data patterns, and provide equations to obtain unbiased estimates by averaging over the various missing data patterns.

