### Secondary outcomes

Secondary alcohol outcomes include changes in the full AUDIT [22] score and drinking data collected using a calendar based Timeline Followback [35] for the month (28 days) prior to the follow up interview. Secondary IPV outcomes include changes in the Composite Abuse Scale [36] and measures of the frequency and severity of IPV from the CTS2S.

Other health-related outcomes include: self-rated health, quality of life, sleep, and relationship satisfaction. For these secondary outcome measures collected at baseline, 3, 6, 9, and 12 months, Hierarchical Linear Models (HLM) will be implemented to compare the intervention and assessed control groups. Variables that show significant differences between the treatment groups at baseline will be included as covariates in the model.

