For the power analyses, we specified a Type-I error level (alpha-level) of 0.025 (splitting alpha between the two primary outcomes of heavy drinking days and IPV incidents). For heavy drinking outcomes, we derive a randomized sample size of 199 per group to achieve at least 80% power to detect a significant effect in the rate of change between groups with attrition/missing data of 30% during the first 12 weeks of treatment. For IPV primary outcomes, this size sample (199 per group) yields power of 93.7% for detecting a clinically significant result with 30% attrition/missing data across 12 weeks. Thus, a randomized sample of 240 subjects per group needed for the comparisons with the no contact control group is more than adequate for conducting the primary analyses comparing BIG to the Assessed Control groups.

For the analysis of intervention moderators, we assume that if the moderator variables are measured without error, we need a sample size of 55 to have 80% power to detect a medium effect with an alpha of 0.05. While demographic variables are measured without error, the baseline risk status variables have reliability indices closer to 0.90. Aiken and West [43] argue that the sample size required to reach a power of 80% with an alpha value of 0.05 is slightly more than doubled when reliabilities drop from 1.0 to 0.80. According to these standards, our sample size of 240 per group (accounting for 30% attrition) is more than sufficient to detect a medium effect size for a moderator.

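### The article makes heavy drinking and IPV primary both on the 12-week weekly phone series and at the 3-, 6- and 12-month interviews, but elsewhere treats the interview measures as secondary and splits alpha for two 12-week outcomes only

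*Protocol article*

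**What the plan says.** Places that make the interviews part of the primary outcomes:

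- Abstract, Methods and design: the primary outcomes are "assessed weekly by Interactive Voice Response System for 12 weeks and at 3, 6 and 12 months by interviewers blinded to group assignment".
- Study hypotheses: the first hypothesis covers heavy-drinking days and IPV incidents "assessed weekly for 3 months and by follow up interviews at 3, 6, and 12 months", though it does not use the word primary.
- Analysis of intervention and assessed control groups: the groups are compared on primary outcomes "collected via the interactive voice response system for 12 weeks after enrollment and by interview at 3, 6 and 12 months".
- Data management and quality assurance: primary outcome data are said to be spread across the data collection tools, which is the reason given for duplicate entry of all case files.

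Places that point to the weekly interactive voice response (IVRS) data alone:

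- Structured women's health interview: the interview is described as holding measures for secondary outcomes, mediators and moderators.
- Primary outcomes collected by the interactive voice response system: two outcomes are numbered, and the primary model is "Hierarchical Generalized Linear Models (HGLM) to accommodate the clustering of the weekly repeated measures".
- Secondary outcomes: the list includes the full AUDIT score, Timeline Followback drinking, the Composite Abuse Scale and "measures of the frequency and severity of IPV from the CTS2S".
- Power for analyses: alpha is 0.025, obtained by "splitting alpha between the two primary outcomes of heavy drinking days and IPV incidents". Attrition and power for these outcomes are worked out over the first 12 weeks.

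One measure falls between the two groups. Analysis across all three groups describes a single AUDIT item, asked at interview, that gives the frequency of heavy drinking. The secondary list names the full AUDIT score but not this item.

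**The concern.** A two-way alpha split fits two primary tests. If each outcome is also primary at three interviews, there are more than two, and nothing in the article says how alpha is shared among them.

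The two sources cannot simply be taken as one endpoint. The weekly calls count heavy-drinking days and IPV events in the past week. The interview has an AUDIT frequency item and a CTS2S scored in frequency bands over the previous three months.

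What is at stake is the trial's claim. Suppose the 12-week series shows no difference and the 12-month interview does. The abstract and the opening of the two-group analysis would let this be reported as a positive primary result. The secondary outcomes section would not. The mediator analysis is affected too: it goes ahead only if the groups differ significantly on IPV and drinking, with no statement of which source or visit decides.

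**Working it through.** **Inputs**

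- Alpha per primary outcome: 0.025, two outcomes (Power for analyses).
- Interview times: 3, 6 and 12 months (abstract; Analysis of intervention and assessed control groups).
- Randomized per group 240, attrition 30% (Power for analyses).
- Heavy drinking at week 12: 3.5 against 1.5 days/month, a difference of 2 days/month or 0.5 days/week at four weeks to the month; SD 1.25 on the weekly scale (Power for analyses).
- Correlation between tests of the same outcome: not given. Assumed 0.5 to 0.9, equal for all pairs, with the two outcomes independent of each other.

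**1. The plan's own figure.** Two tests at 0.025: 2 × 0.025 = 0.05. If independent, 1 − 0.975² = 0.049. The split reproduces an implied total of 5%.

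**2. If the interviews are also primary, each test at 0.025.** The article gives no number of interview tests, so two counts are shown. The bound is m × 0.025, and the value under independence is 1 − 0.975^m.

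- Four tests (two outcomes, each with one weekly comparison and one combined interview comparison): bound 4 × 0.025 = 0.10; independent 1 − 0.975⁴ = 0.096.
- Eight tests (two outcomes, each with the weekly series and separate tests at 3, 6 and 12 months): bound 8 × 0.025 = 0.20; independent 1 − 0.975⁸ = 0.183.

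**3. With correlation.** Let q be the null probability that none of the tests within one outcome is significant. The family-wise error is then 1 − q². Simulation of correlated normal test statistics (400,000 draws) gives:

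| Within-outcome correlation | Four tests | Eight tests |
|---|---|---|
| 0.5 | 0.091 | 0.158 |
| 0.7 | 0.084 | 0.134 |
| 0.9 | 0.071 | 0.096 |

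Numerical integration of the same model agrees to within 0.001. A modest correlation between the two outcomes lowers these values only slightly. The lowest value in any case tried was about 0.064 (four tests, correlation 0.95).

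**4. Price of keeping the interviews primary.** Bonferroni at 5% needs 0.05/4 = 0.0125 or 0.05/8 = 0.00625 per test. With 240 × 0.7 = 168 evaluable per group, a simple comparison of week-12 means has standard error 1.25 × √(2/168) = 0.136, so the standardized difference is 0.5/0.136 = 3.67. Power for heavy drinking is then about 92% at 0.025, 88% at 0.0125 and 82% at 0.00625. This is a simplification of the article's rate-of-change calculation and is used only to show the relative loss for the weekly outcome. The article gives no effect sizes for the interviews.

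**The case against.** A reader might infer that the plan fails to hold family-wise error at 5%, or that it runs at about 18%. The documents do not support that. The 0.025 is given for the power analyses, a 5% family-wise level is implied by the split but never stated, and no section sets an alpha or a number of tests for interview data. The section that defines and models the primary outcomes names exactly two, both weekly. On that reading the split is right as it stands. The 18% also needs eight separate, independent tests. The planned approach to repeated measures is longitudinal modelling, and measures of one construct in the same women are correlated, the more so because the 3-month interview looks back over much the same period as the weekly calls.

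It can also be said that the abstract, the hypothesis and the opening sentence of the two-group analysis only describe when data are collected, and that a testing order is commonly left to the analysis plan.

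The first argument stands: the inflation is conditional. The second does not remove the point. The abstract and the opening of the two-group analysis attach the word primary to both sources, and the data management section says primary outcome data lie across the tools. This is a conflict between statements in the article, not a missing detail. The recall period of Timeline Followback (28 days) is no evidence of a competing primary measure, because that instrument is expressly secondary.

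**Conclusion.** The point holds as an internal contradiction. The article calls heavy drinking and IPV primary on two data sources, treats the interview measures as secondary elsewhere, leaves the interview AUDIT heavy-drinking item unclassified, and provides a model, power and alpha for the two 12-week outcomes only.

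The effect on error depends on which reading is used:

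- Weekly outcomes only: total alpha 5%, no inflation.
- Interviews also tested as primary at 0.025: at most 10% for four tests or 20% for eight, and about 7-9% or 9-16% at within-outcome correlations of 0.5-0.9.

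The test counts and correlations are assumptions, and the article prescribes none of them. What does not depend on them is that the same set of results could be reported as a positive primary finding under one section and as a secondary finding under another. It should be settled before the outcome data are analysed.

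**What to change.** Name the two 12-week weekly comparisons (heavy-drinking days; IPV events) as the only primary tests, each at 0.025, as powered. In the abstract, the first hypothesis and the opening of the two-group analysis, label all 3-, 6- and 12-month interview versions secondary. Add the interview AUDIT heavy-drinking item to the secondary list, and bring the data management sentence into line. State which result triggers the mediator analysis.

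If the investigators want interview results to stay primary, they should fix the number of interview tests and extend the alpha allocation, or a fixed testing order, to them.

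The first option changes wording only: no test, model, sample size or alpha moves. Its small cost is that durability at 6 and 12 months becomes a secondary claim. The second keeps that claim primary. With Bonferroni, it lowers week-12 power for heavy drinking from about 92% to 88% (four tests) or 82% (eight), under the simplified calculation above. The article reports follow-up as still running, so either change can be made before analysis.
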